### Trial Status

The study was started in November 2019, and initially included 24 medical centers from all 13 regions of Jiangsu Province (Table 6). Due to the COVID-19 pandemic (from February 2020 to July 2020), study progress was significantly delayed. In August 2020, another three medical centers from Jiangsu Province and two from Anhui Province joined the study, with the agreement of the members of the Data Safety and Monitoring Board and a common end date of December 30, 2021 was defined. The number of target subjects for each center is determined based on the number of daily CCTA examinations and each centers requests.

**Table 6 T6:** Detail information of the medical centers.

**No**.	**Centers**	**Principal Investigator (PI)**	**Target number of subjects**
1	Jinling hospital	[name]	1,000
2	Nanjing first hospital	[name]	1,000
3	Taizhou people's hospital	[name]	500
4	The first affiliated hospital of nanjing medical university	[name]	500
5	The affiliated wuxi people's hospital of nanjing medical university	[name]	500
6	Affiliated hospital of jiangnan university	[name]	500
7	Subei people's hospital of jiangsu province	[name]	500
8	The first affiliated hospital of soochow university	[name]	500
9	The affiliated hospital of xuzhou medical university	[name]	500
10	The first affiliated hospital of anhui medical university^*^	[name]	500
11	Affiliated hospital of nantong university	[name]	300
12	The affiliated huai'an No.1 people's hospital of nanjing medical university	[name]	300
13	Third affiliated hospital of soochow university	[name]	300
14	The affiliated changzhou No.2 people's hospital of nanjing medical university	[name]	300
15	The second affiliated hospital of nanjing medical university	[name]	200
16	The second affiliated hospital of nantong university	[name]	200
17	The first affiliated hospital of kangda college nanjing medical university	[name]	200
18	Jiangsu province official hospital	[name]	200
19	Affiliated hospital of jiangsu university	[name]	200
20	The affiliated suqian first people's hospital of nanjing medical university	[name]	200
21	The affiliated wujin hospital of jiangsu university	[name]	200
22	Qinhuai medical region of jinling hospital	[name]	200
23	Hai'an city people's hospital	[name]	200
24	Yancheng No.1 hospital	[name]	200
25	The huaihai affiliated hospital of xuzhou medical university	[name]	200

### Data Analysis

According to the Kolmogorov-Smirnov test, continuous data will be categorized as normally or non-normally distributed data. Mean ± SD will be used to express the quantitative variables for uniformity of presentation, regardless of the distribution. Independent sample *t*-tests, paired *t*-tests, or ANOVA tests will be conducted for the comparison of normally distributed continuous data, as appropriate. The difference analysis of non-normally distributed data will be performed by using the non-parametric test. Categorical variables will be expressed as presented as numbers and frequencies or percentages. Pearson's chi-squared test or the likelihood ratio will be used to compare the differences of categorical data between groups, as appropriate. Univariate and multivariate Cox proportional hazard models will be performed to calculate the hazard ratio (HR) with a 95% CI and to estimate the association between variables and the hazards of MACE. Kaplan-Meier plots with the log-rank tests will be generated to estimate cumulative rates of MACE. The receiver operating characteristics (ROC) curve analysis will be performed to determine the optimal cut-off values of quantitative data. The area under the curve (AUC) for each model will be compared. The patient's annual total cardiac cost will be compared using the non-parametric Wilcoxon rank-sum test or a two-sample *t*-test. Intraclass correlation coefficient (ICC) and Spearman correlation coefficient will be used to assess the inter- and intra-observer agreement. Considering the selection bias and potential heterogeneity between 29 centers, a center effect analysis will be performed. If there is a central effect, a stratified analysis and sensitivity analysis will be performed, or it will be adjusted as a random factor. A *p* ≤ 0.05 is considered statistically significant.

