## Abstract

Coronary artery disease (CAD) is a major contributor to morbidity and mortality worldwide. Myocardial ischemia may occur in patients with normal or non-obstructive CAD on invasive coronary angiography (ICA). The comprehensive evaluation of coronary CT angiography (CCTA) integrated with fractional flow reserve derived from CCTA (CT-FFR) to CAD may be essential to improve the outcomes of patients with non-obstructive CAD. China CT-FFR Study-2 (ChiCTR2000031410) is a large-scale prospective, observational study in 29 medical centers in China. The primary purpose is to uncover the relationship between the CCTA findings (including CT-FFR) and the outcome of patients with non-obstructive CAD. At least 10,000 patients with non-obstructive CAD but without previous revascularization will be enrolled. A 5-year follow-up will be performed. The primary endpoint is the occurrence of major adverse cardiovascular events (MACE), including all-cause mortality, non-fatal myocardial infarct, unplanned revascularization, and hospitalization for unstable angina. Clinical characteristics, laboratory and imaging examination results will be collected to analyze their prognostic value.

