#### Qualitative Evaluation of the Coronary Plaque

According to previous studies, four signs of coronary artery plaques on CCTA will be recorded as HRP features, namely, low-density plaque (LAP), PR, punctate calcification (SC), and napkin ring sign (NRS) (26). LAP is defined as the plaque component with an attenuation of <30 HU. RI > 1 indicates PR. SC is defined as any discrete calcification less than or equal to 3 mm in length and occupying less than or equal to 90° arc when viewed in the short axis. NRS is recognized as a central low attenuation plaque with a peripheral rim of higher attenuation of the non-calcified plaque.

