### CT-FFR Measurements

All CT-FFR values will be calculated by using an automated software (“Shukun-FFR” software from Shukun [Beijing] Technology Co., Ltd). The “Shukun-FFR” software consists of two main components, the coronary arteries segmentation model and the computational fluid dynamics (CFD) simulation model. Specifically, a modified V-Net is first used to to segment coronary arteries from the CCTA image firstly (30). Then, we adopt prior knowledge to name vascular branches based on additional anatomical rules, using previous vessel segmentation results as input. The final reduced-order CFD model is applied to compute the flow and pressure of blood and calculate CT-FFR values automatically for all points along coronary arteries. CT-FFR values will be determined for coronary arteries ≥1.5 mm in diameter in the core laboratory by two cardiovascular radiologists (observers A and B). The automatically identified coronary plaques and the degree of lumen stenosis will be verified by another well-experienced observer. Observer A will carry out measurements two times separately (recorded as A1, A2). The time interval between the two measurements is 2 weeks to eliminate the effect of memory; observer B will measure one time (recorded as B). CT-FFR values will be measured at the proximal, distal, and 20 mm distal to the stenosis and the end of the target vessel (at least 1.5 mm diameter). CT-FFR ≤ 0.80 indicates the hemodynamic significance of coronary stenosis. Patients with CT-FFR ≤ 0.80, which is 20 mm distal to the stenosis, are deemed to have lesion-specific ischemia. Patients without lesion-specific ischemia but with CT-FFR ≤ 0.80 at the end of the target vessel are deemed to have distal vessel ischemia.

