## Conclusion

The China CT-FFR Study-2 is a prospective, observational, multicenter registry study. At least 10,000 patients with non-obstructive CAD will be enrolled from 29 medical centers in China. Baseline clinical information and CCTA findings (such as CT-FFR) will be collected. A 5-year follow-up will be performed by phone contact to ascertain the outcomes of patients. To the best of our knowledge, this is the largest prospective observable study to explore the relationship between CT-FFR and prognosis in China. Based on the excellent performance of CT-FFR for diagnosing myocardial ischemia and its predictive value for future risk of MACE, we believe that the China CT-FFR Study-2 will be helpful to provide unique risk stratification of patients with non-obstructive CAD.

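### ROC-optimal cut-offs taken from the cohort need out-of-sample testing: tested at 0.05 in the same patients, a useless marker would pass about 7% to 47% of the time, depending on the rule

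*Protocol article*

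**What the plan says.** The Data Analysis section of the protocol article gives the cut-off rule in one sentence: "The receiver operating characteristics (ROC) curve analysis will be performed to determine the optimal cut-off values of quantitative data". It names no optimality criterion, no direction and no list of variables.

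The same section provides the tests. For association: "Univariate and multivariate Cox proportional hazard models will be performed to calculate the hazard ratio (HR) with a 95% CI". For group comparison: "Kaplan-Meier plots with the log-rank tests will be generated to estimate cumulative rates of MACE". The significance criterion is p ≤ 0.05. No split sample, resampling or correction for choosing the cut-off is stated. The Discussion concedes that external verification is lacking.

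Some variables have categories set in advance. The plaque evaluation sections fix groups for the Agatston score, the arc of calcification, CAD-RADS and the remodeling index ("RI > 1 indicates PR"). CT-FFR Measurements fixes "CT-FFR ≤ 0.80 indicates the hemodynamic significance of coronary stenosis" and builds lesion-specific and distal vessel ischemia on that value. No categories are given for plaque volume and its components, plaque burden, minimal lumen diameter (MLD), minimal lumen area (MLA) or plaque length.

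**The concern.** A ROC-optimal cut-off is the point at which the two groups differ most, on the chosen criterion, in their outcome in this cohort. A log-rank or Cox test of those groups in the same patients treats the cut-off as if it had been known beforehand. The p-value is then too small and the hazard ratio too far from 1.

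The second aim is the value of CT-FFR beyond clinical and anatomical factors, and AUCs are to be compared between models. Anatomical comparators cut at outcome-tuned points would look better in this cohort than they would elsewhere, and would also lose information by being dichotomised. Either effect can distort the incremental-value comparison. The Discussion expects the registry to inform future randomised trials, so cut-offs that do not reproduce could be carried forward.

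**Working it through.** **Inputs from the article.** At least 10,000 patients, 5-year follow-up, p ≤ 0.05, log-rank and Cox tests. It gives no false-positive rate or expected MACE rate, so there is no figure to reproduce.

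**Assumptions.** Two-sided test (|Z| > 1.96); 5-year MACE risk of 3%, 5%, 10% or 20%; a continuous marker without ties, independent of MACE; no loss to follow-up.

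**Method.** Order the N patients by the marker and let E be the number of events. For a cut after the k-th patient, with t = k/N:

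- TPR = (events among the first k)/E
- FPR = (non-events among the first k)/(N − E)
- J = TPR − FPR
- Pearson Z = J·√[E(N − E)/N] / √[t(1 − t)]

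Choose the cut by each rule, then test it on the same data:

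- Youden, free direction: maximise |J|.
- Youden, fixed direction: maximise J.
- Closest to (0,1): minimise (1 − TPR)² + FPR².

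**Results.** False-positive rate (%) for a null marker, N = 10,000; 5,000 replicates per cell, 4,000 in the last row.

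| Rule | MACE 3% | 5% | 10% | 20% |
|---|---|---|---|---|
| Cut fixed beforehand | 5.0 | 4.9 | 5.0 | 5.0 |
| Youden, free direction | 45.6 | 45.2 | 44.9 | 44.3 |
| Youden, direction from the AUC | 44.3 | 43.8 | 43.7 | 43.3 |
| Youden, direction fixed | 27.2 | 26.8 | 27.3 | 26.0 |
| Closest to (0,1), direction from the AUC | 16.2 | 14.5 | 13.5 | 12.4 |
| Closest to (0,1), direction fixed | 8.6 | 7.6 | 7.3 | 5.7 |

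The simulation error is at most √(0.45 × 0.55/5,000) = 0.7 points for the 5,000-replicate rows. A separate simulation at 5% and 10% MACE gave 45–47%, 26–28% and 7–8% for Youden free, Youden fixed and closest-to-(0,1) fixed. A further run over 3–20% MACE gave 43–46% and 25–27% for the two Youden rules.

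**Log-rank check.** Event times were exponential with rate −ln(1 − p)/5, N = 10,000, 3,000 replicates. At MACE 5% and 10%:

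- Youden, free direction, same data: 45.4% and 45.1%.
- Fixed cut: 4.9% and 4.9%.
- Cut chosen on one half and tested on the other: 5.3% and 4.8%.

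**Analytic cross-check.** The Miller–Siegmund approximation for a maximally selected test over the central 1 − 2ε of values is 4φ(z)/z + φ(z)(z − 1/z)·ln[(1 − ε)²/ε²]. With z = 1.96, φ(z) = 0.0584 and ε = 0.10, this is 0.119 + 0.0847 × 4.394 = 0.49. Simulation of that test gave about 48%.

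**Sample size.** At N = 1,000 and MACE 10%, Youden with free direction gave 43%. A large cohort does not remove the problem.

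**Size of the spurious effect.** With Youden and free direction at N = 10,000, the median risk ratio for a null marker was 1.27, 1.20 and 1.13 at MACE 3%, 5% and 10%.

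**Several markers.** For three independent null markers, the chance of at least one false positive is 1 − 0.55³ = 83% at 45% each, against 1 − 0.95³ = 14% at the nominal level. Plaque measures are correlated, so this is an illustration only.

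**The case against.** Four points are fair.

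First, a reader might infer that the article commits to testing ROC-derived groups. It does not say so. The ROC sentence follows the Cox and Kaplan-Meier sentences and precedes the AUC comparison, with nothing linking the cut-offs to the tests. Markers could enter the Cox models as continuous variables. This stands, and makes the point conditional. However, Kaplan-Meier curves need groups, and for plaque volume, plaque burden, MLD, MLA and plaque length the ROC step is the only grouping rule given.

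Second, a reader might infer that the plan holds two competing definitions of CT-FFR positivity. The documents do not support that. The ROC sentence speaks of quantitative data and does not name CT-FFR. It neither exempts CT-FFR nor says that it will be re-cut. This is an ambiguity to close, not a contradiction. An analysis at 0.80 keeps its 5% level.

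Third, a reader might take 45% as the error rate of the plan. It belongs to one rule, Youden with free direction. Fixing the direction is natural for CT-FFR, where lower is worse, and brings Youden to about 27%. The closest-to-(0,1) rule with fixed direction is only slightly above 5%.

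Fourth, this is a condensed article with an exploratory aim. The criterion, variable list and validation may be in a fuller plan. That silence is therefore not the finding. What remains is a method the article itself states, which gives anti-conservative results if followed as written.

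**Conclusion.** The point holds in conditional form. The article commits to cut-offs derived from the cohort, beside log-rank and Cox tests at 0.05, and for several plaque measures offers no other grouping. If those cut-offs are tested in the patients who produced them, the false-positive rate for a useless marker is about 44–47% (Youden, free direction), 26–28% (Youden, direction fixed) or 7–16% (closest to (0,1), depending on how direction is set, and nearer 6% at the mild end if MACE reaches 20%). These figures rest on N = 10,000, a two-sided test, MACE of 3–20%, an untied continuous marker and no loss to follow-up. The Youden figures hardly depend on the event rate.

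No error is shown in the analysis of CT-FFR at its stated 0.80 threshold. The change is worth making because it is cheap and protects the comparison of CT-FFR with anatomical markers.

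**What to change.** Amend the Data Analysis section to state that:

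- CT-FFR is analysed at the article's own ≤ 0.80 definitions (lesion-specific and distal vessel ischemia) and as a continuous variable, and is not re-cut by ROC.
- The other quantitative markers enter the Cox models as continuous terms, allowing for non-linearity.
- Any ROC cut-off is exploratory, with its criterion and direction named in advance.
- The p-value, hazard ratio and performance of such a cut-off are reported only from held-out centres or cross-validation; otherwise its p-value is adjusted for cut-off selection.

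With 29 centers, holding out centers is feasible. No new data are needed. The cost is a little more analysis work, and some exploratory cut-offs lose their nominal p-values.

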### Primary Endpoints

The primary endpoint is the occurrence of MACE at follow-up, defined as a composite of all-cause death, non-fatal MI, unplanned revascularization (at least 60 days after the CCTA examination), and hospitalization for unstable angina. Death cases consist of cardiovascular death, non-cardiovascular death, and undetermined cause of death. Cardiovascular death includes death attributable to sudden cardiac death, acute MI, heart failure, cardiovascular bleeding, stroke, cardiovascular procedure, and other cardiovascular causes, such as pulmonary embolism. When a definite non-cardiovascular cause is documented, a cardiovascular reason for death could be excluded. Non-fatal MI consists of ST-segment elevation myocardial infarction (STEMI) and non–STEMI. Unstable angina is defined as the symptoms of ischemic chest pain at rest, and the final diagnosis is myocardial ischemia with objective evidence but without elevation of cardiac biomarkers. For the primary endpoints, the first occurrence timepiont of any one of the above events will be recorded. The follow-up duration is recorded as the interval from baseline CCTA examination to the day of follow-up.

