### Secondary Endpoints

Secondary endpoints include cardiovascular death, atrial fibrillation, non-fatal MI, non-fatal stroke, unplanned revascularization, hospitalization for unstable angina, medication adjustment, invasive or non-invasive cardiovascular tests, cumulative radiation exposure from all cardiovascular tests, and total cardiac costs. Medication adjustment includes the increase or decrease of the drug dose and the new addition or discontinuation of medications. For the secondary endpoints, the time of the occurrence for any one of the above events should be recorded.

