### Follow-Up

Telephone follow-up will be performed for each enrollee annually by the follow-up team of each medical center until the completion of the 5-year follow-up. The follow-up team in each center includes at least one nurse, one cardiovascular radiologist, and one cardiovascular physician. The follow-up team will first contact the patient via a phone call. If it is unsuccessful, the personal contact will be called for updated information. After documentation of three unsuccessful attempts (on three different days over 1 month) by the follow-up team, a subject will be considered lost to telephone follow-up. If the outcome of this subject cannot be traced through the medical record system, the subject will eventually be deemed to be lost to follow-up. The follow-up team of the core laboratory will randomly select 10% of the subjects from each other medical center for review to confirm the authenticity of the follow-up data.

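### The cost endpoint is a total with no time window in one section and a yearly figure in another, and the named tests make no allowance for follow-up cut short by death or loss

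*Protocol article*

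**What the plan says.** Protocol article, Secondary Endpoints: the list ends with "cumulative radiation exposure from all cardiovascular tests, and total cardiac costs". No time window or unit is attached to cost.

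Protocol article, Data Analysis: "The patient's annual total cardiac cost will be compared using the non-parametric Wilcoxon rank-sum test or a two-sample" *t*-test. The sentence names no comparison groups and does not say how the yearly figure is formed.

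The same article makes clear that follow-up will differ between patients:
- Follow-Up: "Telephone follow-up will be performed for each enrollee annually by the follow-up team of each medical center until the completion of the 5-year follow-up". A patient who cannot be reached, and whose outcome cannot be traced in the records, is a recognised category: "the subject will eventually be deemed to be lost to follow-up".
- Primary Endpoints: the outcome is "defined as a composite of all-cause death, non-fatal MI, unplanned revascularization" and hospitalization for unstable angina, so deaths are expected.
- Primary Endpoints: "The follow-up duration is recorded as the interval from baseline CCTA examination to the day of follow-up", which is specific to each patient.

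**The concern.** A cumulative total and a yearly figure give the same comparison only if everyone is observed for the same time. Otherwise they are different quantities, and the article lists one and analyses the other.

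Both named tests treat each patient's value as complete. For MACE the same section uses Cox and Kaplan-Meier methods, which do allow for censoring; the cost sentence has no counterpart. If CT-FFR predicts MACE, as the study hypothesises, death will end follow-up more often in the CT-FFR-positive group. If loss also differs between groups, part of any cost difference is simply a difference in observed time. The Discussion takes up conflicting cost results for CT-FFR, so this comparison will be read even though it is secondary.

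**Working it through.** **Inputs.** The article supplies no cost, cost SD, death rate, loss rate or expected cost gap, so there is no figure to reproduce. Everything below is assumed. The groups are taken as CT-FFR ≤ 0.80 versus > 0.80, the cut-off in CT-FFR Measurements. Routine cost is 1 unit per year and times to death, first event and loss are exponential.
- Model A: event cost 10; yearly death 1.6% vs 0.8%; yearly event 2.5% vs 1%; cost at death 5 or 0.
- Model B: event cost 20; yearly death 0.8% and event 2% in the lower-risk group, both multiplied by 1.5 or 2 in the other; cost at death 15 or 0.

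**Raw totals.** Let m, e and l be the yearly death, event and loss rates, and A(h) = (1 − exp(−5h))/h. The mean observed 5-year total is

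A(m+l) + event cost × e × A(e+m+l) + death cost × m × A(m+l).

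Model A, death cost 5:
- No loss: positive 4.805 + 10 × 0.1130 + 5 × 0.0769 = 6.320; negative 4.901 + 10 × 0.0478 + 5 × 0.0392 = 5.576. True gap 0.744, ratio 1.13.
- Equal loss, 2% or 5% per year: the ratio stays at 1.13, and the absolute gap falls to 0.96 or 0.89 of the true gap.
- Loss 5% vs 2%: positive 4.259 + 10 × 0.1004 + 5 × 0.0681 = 5.604; negative 4.666 + 10 × 0.0455 + 5 × 0.0373 = 5.308. Gap 0.296, and 0.296/0.744 = 0.40 of the true gap.

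The same formula with 5% vs 2% loss gives the fraction of the true gap retained:

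| Model | No cost at death | Cost at death |
|---|---|---|
| A | 0.26 | 0.40 |
| B, hazard ratio 1.5 | 0.33 | 0.44 |
| B, hazard ratio 2 | 0.60 | 0.66 |

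For the rank-sum test, the relevant quantity is the probability that a positive patient's cost exceeds a negative patient's. In model B with death cost and hazard ratio 1.5, simulation gives 0.53 for complete 5-year cost and 0.47 for raw totals under 5% vs 2% loss: the direction reverses. At hazard ratio 2 the groups come out about level.

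**Total divided by own follow-up (one possible reading of the yearly figure).** Costs that accrue while a patient is observed grow roughly in proportion to observed time, so dividing by that time does little harm. A cost incurred at death is different, because it arrives exactly when follow-up stops. If the divisor has a minimum of f years, its average contribution is multiplied by about 1 + ln(5/f) (ignoring the small attrition term):
- f = 1 year: 1 + ln 5 = 2.6
- f = 3 months: 1 + ln 20 = 4.0
- no minimum: ln(5/f) grows without limit, so the mean does not settle.

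Simulated mean gap relative to the true 5-year gap divided by 5:
- No cost at death: 1.02 with equal mortality; 1.24 to 1.26 with twofold mortality.
- Twofold mortality and death cost 5: 1.56 with a 1-year minimum, 2.03 with a 3-month minimum. Other settings with a 3-month minimum ran from 1.17 to 2.42. A setting with a true gap near zero (0.017) gave 9.2, where a ratio means little.
- Cost at death, no minimum: from −0.36 to about 7, driven by a few very early deaths.

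**The case against.** The harmful reading of the yearly figure is not in the text. It may equally mean the cost in each follow-up year, which suits the annual calls, and then the inflation does not arise in that form. That stands. It leaves unsaid how years cut short are treated and how five yearly figures relate to the single listed total.

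The article names the rank-sum test first, and ratios of means say nothing about it. With no loss in model B with death cost, the rank probability is 0.530 for both true and annualised cost at hazard ratio 1.5, and 0.555 versus 0.556 at hazard ratio 2. That stands for no loss, and nearly so for equal loss. It fails for raw totals under unequal loss, as shown above.

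This is one of about ten secondary endpoints in a condensed article, and details of cost censoring often sit in the full plan. That lowers the weight. It does not remove the point, because the article itself states the cost variable and its tests, and the variable differs from the listed endpoint.

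A reader might infer that annualising roughly doubles the cost gap. The documents contain nothing to support a single factor. In model B, the excess doubles only with a 15-unit cost at every death and a one-day minimum follow-up; without the death cost the ratios move only from 1.12 to 1.13 and from 1.23 to 1.25. Such a charge is also doubtful for a cardiac cost, since non-cardiovascular deaths are counted.

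**Conclusion.** The point holds in a limited form. The two sections name different cost quantities, neither has a defined time window, and the named tests do not allow for the incomplete follow-up that the article foresees.

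The size depends on assumptions. Raw totals preserve the ratio under equal loss and retain about 0.3 to 0.7 of the true gap under an assumed 5% versus 2% yearly loss, with a possible reversal of the rank-sum direction. Dividing by own follow-up, if that is meant, moves the mean gap by a factor of about 1.0 to 1.26 with no cost at death, mostly 1.3 to 2 with such a cost and a minimum divisor, and unpredictably without one.

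It would be too strong to say that both versions are always distorted: totals keep the ratio under equal loss, and the annualised gap is nearly unbiased (1.02) with equal mortality and no cost at death. Nor does the point extend to cumulative radiation exposure, for which the Data Analysis section states no analysis. The primary endpoint is unaffected.

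**What to change.** Use one definition in Secondary Endpoints and Data Analysis: mean cumulative cardiac cost over 5 years from the baseline CCTA, with no accrual after death, so that death ends cost and is not treated as censoring. Name the groups to be compared. Estimate the mean in each group with inverse-probability-of-censoring weights applied to yearly cost increments, so that partly followed patients contribute the years they have, and give the difference with a bootstrap confidence interval. Any yearly figure should be that estimate divided by 5, not an average of per-patient cost/follow-up ratios.

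The cost is a couple of sentences and some programming, with no extra patients. Costs must be recorded by year of follow-up, which the annual calls allow. The weights also assume that loss is explained by what has been measured, and this should be stated.

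### Spearman's coefficient is listed beside the ICC as a measure of observer agreement, but it measures rank association and cannot register a constant difference between readers

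*Protocol article*

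**What the plan says.** The Data Analysis section gives one sentence to reproducibility: "Intraclass correlation coefficient (ICC) and Spearman correlation coefficient will be used to assess the inter- and intra-observer agreement". It names both coefficients and does not give the form of the ICC.

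The readings are described under CT-FFR Measurements. For the intra-observer comparison, "Observer A will carry out measurements two times separately (recorded as A1, A2"), with two weeks between the readings. For the inter-observer comparison, "observer B will measure one time (recorded as B"). The values come from software ("All CT-FFR values will be calculated by using an automated software"), and the observers take them at set sites along the vessel. The same section sets a fixed threshold: "CT-FFR ≤ 0.80 indicates the hemodynamic significance of coronary stenosis". It uses that threshold to define lesion-specific ischemia and distal vessel ischemia.

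No mean difference, limits of agreement or categorical agreement at 0.80 is named for the observer comparison. Paired t-tests appear in Data Analysis only in a general list of tests that "will be conducted for the comparison of normally distributed continuous data, as appropriate". They are not tied to the readers.

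**The concern.** Agreement asks whether two readings give the same value. Spearman's coefficient asks whether they put patients in the same order. If observer B reads every vessel 0.03 lower than observer A, the order is unchanged and the coefficient does not move, yet the two observers disagree about every patient. The difference matters here because CT-FFR is read against a fixed cut-off, so a uniform offset turns directly into different ischemia labels.

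What is at stake is how the reproducibility result is read. A Spearman value close to 1, reported as evidence of agreement, would add reassurance that it cannot support. It would stand next to an ICC that may itself look acceptable.

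**Working it through.** The article reports no reliability figure, so there is no stated number to reproduce. The check asks how each statistic behaves when one reading is shifted.

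**Inputs from the document.** The cut-off of 0.80, the readings A1, A2 and B, and the two named coefficients.

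**Assumptions, not in the document.** CT-FFR is normal with mean 0.87 and SD 0.06. The second reading equals the first minus a constant shift b, plus random error with SD 0.01. The shift b is 0, 0.02, 0.03 or 0.05.

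**Step 1: variances.** First reading: 0.06² = 0.0036. Second reading: 0.0036 + 0.0001 = 0.0037. Their mean is 0.00365 and the covariance is 0.0036. None of these depends on b.

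**Step 2: Spearman.** The Pearson correlation is r = 0.06/√0.0037 = 0.986. For normal data Spearman = (6/π) × arcsin(r/2) = 0.985. The shift does not enter, so the value is the same for every b.

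**Step 3: ICC.**
- Consistency form: 0.0036/0.00365 = 0.986, also free of b.
- Absolute-agreement form: 0.0036/(0.00365 + b²/2). For b = 0.02 this is 0.0036/0.00385 = 0.935; for b = 0.03, 0.0036/0.00410 = 0.878; for b = 0.05, 0.0036/0.00490 = 0.735.
- One-way form: (0.0036 − b²/4)/(0.00365 + b²/4). For b = 0.02 this is 0.00350/0.00375 = 0.933; for b = 0.03, 0.003375/0.003875 = 0.871.

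**Step 4: class at 0.80.** First reading positive: Φ((0.80 − 0.87)/0.06) = Φ(−1.167) = 12.2%. Second reading positive at b = 0.03: Φ((0.80 − 0.87 + 0.03)/0.0608) = Φ(−0.658) = 25.5%. The share classed differently is p1 + p2 − 2·p11, where p11 is the bivariate normal probability that both readings are positive. At b = 0.03, p11 is 12.2%, which gives 13.4%. Kappa is (observed − chance agreement)/(1 − chance agreement) = (0.866 − 0.685)/(1 − 0.685), about 0.58.

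| Shift | Spearman | ICC, consistency | ICC, absolute agreement | Positive, second reading | Change class | Kappa |
|---|---|---|---|---|---|---|
| 0 | 0.985 | 0.986 | 0.986 | 12.5% | 2.7% | 0.87 |
| 0.02 | 0.985 | 0.986 | 0.935 | 20.6% | 8.4% | 0.70 |
| 0.03 | 0.985 | 0.986 | 0.878 | 25.5% | 13.4% | 0.58 |
| 0.05 | 0.985 | 0.986 | 0.735 | 37.1% | 25.0% | 0.38 |

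Random error alone accounts for 2.7%, so most of the 8.4% and 13.4% is due to the shift.

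**Step 5: sensitivity.** A simulation of 200,000 pairs per setting used means of 0.85 and 0.88 and SDs of 0.06 to 0.10. Without reader error, a shift of 0.02 changes the class of 6% to 11% of patients with an absolute-agreement ICC of 0.95 to 0.98. A shift of 0.03 changes 10% to 17% with an ICC of 0.89 to 0.96. A shift of 0.05 changes 17% to 30% with an ICC of 0.74 to 0.89. With error SD 0.02 in each reading, Spearman lies between 0.89 and 0.96 depending on the SD, and within each setting it is the same at every shift.

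**Step 6: what a direct summary shows.** At b = 0.03 the paired differences have mean 0.03 and limits of agreement 0.03 ± 1.96 × 0.01, that is 0.010 to 0.050. Zero lies outside these limits, so the offset is visible at once.

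**The case against.** The strongest reply is that the same sentence also plans an ICC. A reader might infer from the use of Spearman that the plan could not detect a systematic shift between readers. The document does not support that. An absolute-agreement or one-way ICC falls from 0.986 to about 0.73 or 0.70 at a 0.05 shift in the scenario above. Only a consistency ICC would miss it, and the article does not name that form. Leaving the form to a fuller document is normal for an article and is no fault. This reply stands. It does not rescue Spearman, and it leaves the point that at 0.02 to 0.03 even the absolute-agreement ICC can look good while a noticeable share of patients change class.

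A second reply is that nothing shows a shift of this size exists. The software calculates values at all points along the arteries, the measuring sites are specified, and another observer verifies plaques and stenosis. This may well make a large uniform offset less likely, although the choice of site can still introduce differences. It would therefore be wrong to infer that many patients will be misclassified.

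A third reply concerns consequence. A reader might infer that the binary class is the exposure in the outcome models, so that poor agreement undermines the MACE result. The article does not say this. Its aim refers to the predictive value of CT-FFR without fixing a binary form, the Cox models are described for variables in general, and ROC cut-offs are planned for quantitative data. No threshold for the ICC or Spearman is set, and no outcome analysis depends on one. This reply stands too.

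The listed paired t-tests could test for a mean difference between readers, but the text does not assign them to that use.

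**Conclusion.** The point holds in a narrow form. Spearman's coefficient is named for a purpose it cannot serve, and that is an error in what the text states, whatever a fuller plan may add. Its insensitivity to a constant shift is exact and needs no assumption.

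The size of the practical effect does rest on assumptions: the mean, the SD, the error and above all the existence of a shift of 0.02 to 0.03. Given those in the main scenario, roughly 8% to 13% of patients change class while the absolute-agreement ICC remains at about 0.94 to 0.88. The percentages illustrate why bias and categorical agreement are worth reporting; they do not predict what this study will find. The matter is minor, confined to the reproducibility sub-analysis.

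**What to change.** In Data Analysis, remove Spearman's coefficient as a measure of observer agreement and state that the planned ICC is the absolute-agreement form. For A1 against A2 (intra-observer) and A against B (inter-observer), add:

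- the mean difference with Bland-Altman limits of agreement;
- per cent agreement and kappa for CT-FFR ≤ 0.80, shown with the proportion positive in each reading, since kappa depends on prevalence.

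If Spearman is kept at all, label it as rank association. The cost is a change of wording and a few extra lines of output. The readings are already planned, so no new measurements, patients or follow-up are needed.
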